
#### Model fit criteria

The following suggested model fit criteria will be used to assess the fit of the latent growth curve model to the data: non-significant model chi-square, CFI above .95, RMSEA below .05–.08, and a SRMR value below .08 [60, 61].

#### Missing data

Every effort will be made to avoid missing data, particularly with respect to our follow-up data points. However, missing data is a common problem in longitudinal research, so it is important to be aware of sources and plan appropriate procedures for accommodating missing data [62]. Missing data can be broadly classified as missing at random or missing not at random and are either ignorable or not ignorable. To assess type of missing data, we will employ various tests for the effects of missing data on our sample (e.g., homogeneity of growth parameters across different patterns of missing data and pattern-mixture modeling). There are several methods for dealing with missing data including ignoring missing data and modeling with complete data only. However, this strategy can bias parameter and standard errors by utilizing smaller proportions of available data and depends on the assumption that data is MCAR [62]. An alternative involves data imputation with multiple imputation [63].

#### Power analysis

As this is a pilot study, the primary outcome is understanding the feasibility of implementing a large-scale trial. For the mixed MANOVA and using G*power 3.1.7 [64, 65] with three groups (*n* = 20 per group) and five repeated measures, using a 10% probability of a type I error (α = .10), and a medium effect (*f* = .25), the power achieved was .55.

To assess power in the LGCM, we conducted a series of Monte Carlo simulations with 1000 replications, to determine sample size for sufficient power to evaluate developmental trajectories of our primary and secondary outcome variables in a sample of 60 participants with AN. We used M*plus* 7.2 software for all simulations [66]. Population parameter estimates were derived using data from our prior longitudinal analyses. We concluded sufficient power only if the simulation resulted in parameter and standard error bias less than 10% and 15%, respectively, coverage close to 95% (i.e., confidence interval includes the population value), and power above .80 for the significant effects [66–68]. Power calculations were based on ability to detect small but meaningful effect sizes for intercept (baseline level) and trend (rate of change) factors [69]. The results supported low bias (< 10%), acceptable parameter coverage values for the intercept (.95) and trend (.944) factors, and sufficient power (>.95).

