### Participants

Participants are male and female adolescents aged 12–18 who present in hospital for treatment of a restrictive eating disorder and at least one caregiver. Only adolescents who have not had prior multidisciplinary treatment for an eating disorder will be included. Inclusion and exclusion criteria are summarized in Table 3.^1^ The total enrollment is anticipated to be 60 adolescents.

**Table 3 Tab3:** Inclusion and exclusion criteria

Inclusion criteria	Exclusion criteria
• Adolescent is between 12 and 18 years of age and living at home with caregiver(s) • Adolescent meets diagnostic criteria for anorexia nervosa (either restricting or binge/purge subtype), or sub-threshold anorexia nervosa according to the DSM-5 criteria • Parent or primary caregiver is willing to participate in CRT + TTP or CRT + FFT sessions (if randomized to either condition) • Consent of all family members who will be participating in treatment • The adolescent is not currently receiving outpatient treatment for the eating disorder (i.e., their first presentation at CHOP)	• Caregiver or adolescent with a co-morbid diagnosis of psychotic disorder, substance dependence, substance abuse, or bi-polar disorder • Caregiver or adolescent with diagnosis of intellectual disability, developmental delay, or autism spectrum disorder • Adolescent with a diagnosis of feeding or eating concerns not elsewhere classified with primary symptoms of bingeing and purging, bingeing without compensatory behaviors, or spitting food with restricting patterns. • Adolescent with diagnosis of avoidant/restrictive food intake disorder • Adolescent or caregiver with acute suicide risk • Concurrent psychosocial treatment for another condition • Adolescent or parent (who will be participating) not fluent in English

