### Outcomes

The primary aim of the study is to evaluate the feasibility and pilot the procedures for an RCT of CRT with a family component delivered during a hospital stay for medical stabilization. Primary outcomes are as follows:Recruitment rates (% of patients admitted who are eligible, % enrolled). Ideally, we will be able to recruit 30% of those eligible and at least four adolescents and their parents a month.Completion rates (% of those enrolled who complete at least 6 sessions). Completion rates will vary based on the medically dictated hospital stay. As we have no control over when an adolescent will be discharged, completion rates will be combined with enrollment rates to determine how many participants would need to be enrolled in a future study (over-enrollment) to ensure the appropriate number of treatment completers.Refusal rates and reasons whyRetention rate (% of those enrolled who completed all assessment points, rate of drop out over 6 months of follow-up). Ideally, we would have a dropout rate < 25%. As adolescents are discharging to various levels of care, we track dropout rates and determine if we have higher rates associated with certain levels of care (e.g., residential treatment).Average length of time to complete measures

We will also pilot procedures and evaluate the following:Ease of record forms (can the study staff use forms effectively and can the interventionist easily record data needed from each CRT session)CRT task adaptations (e.g., are some tasks more difficult for adolescents, are there modifications that need to be made)Staffing needs (are there enough staff to recruit/enroll/assess/and administer CRT?)Acceptably of RCT to medical staff (evaluated through meetings with and feedback from staff (e.g., physicians, nurses, behavioral health)

In addition to piloting the study and assessing feasibility, our secondary goals are to examine relevant outcomes for a fully powered trial. We will examine the following:Willingness of adolescent to engage in treatment post-dischargeAdolescent rate of weight gain post-discharge to 6 monthsParental accommodation in symptoms post-discharge (group differences and over time changes)Changes in set-shifting or central coherence

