#### Efficacy analysis

Although this is a pilot study, we do want to explore whether or not there is a difference between groups. In order to determine differences between those who are randomized to TAU, CRT + FFT, or CRT + TTP, we will conduct a mixed multivariate analysis of variance (MANOVA) with five repeated measures (time: baseline, discharge, 4 weeks post-discharge, 3 months post-discharge, and 6 months post-discharge) as a within-subjects factor and treatment as a three-level between subjects’ factor. We will also evaluate the condition (treatment) × time interaction. We have three quantitative dependent variables: adolescent treatment engagement, post-treatment weight gain, and symptom accommodation. For initial analyses, we will focus on change pre- to 4-week post-discharge. Any post hoc comparisons will involve comparing subsequent assessments to baseline—as they will be simple planned comparisons. This will allow us to retain the most amount of power (i.e., to enable us to reject the false null hypothesis) [57]. We will also set alpha at .10, which will also increase power. Given these parameters, enrolling 60 adolescents would give us an N comparable to prior research using CRT [58].

In addition to the prior analyses, we will also assess developmental trajectories for rate of weight gain post-discharge, treatment engagement post-discharge, and symptom accommodation using latent growth curve modeling (LGCM) with one growth curve analysis for each variable. LGCM is a structural equation modeling method that models repeated observed measures (measured variables) on factors (latent variables) representing random effects [59]. In LGCM, a level factor is used to represent baseline and trend factors are used to represent rate of change across time. Latent variables define the form of rate of change across time (e.g., linear, quadratic, cubic). Factor loadings are fixed to define baseline level and trend. For a linear trend, the factor loadings are set so they increase uniformly with each unit increase in time. Given is a preliminary analysis, these results will allow us to better understand how change occurs over time. Instead of relying on probability values which subject us to increased type II error rates given the small sample size (i.e., low power), we will assess confidence intervals around our estimates to provide information regarding margins of error. All confidence intervals will be 90% confidence intervals given the small sample sizes.

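### The only MANOVA power figure, .55, belongs to a five-occasion test with all 60 complete; the 4-week change that is analysed first has no stated power, and no dropout is allowed for

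*Protocol article*

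**What the plan says.** The Power analysis section of the protocol article describes a calculation for the mixed MANOVA that assumes "five repeated measures, using a 10% probability of a type I error". It takes 20 participants in each of the three arms, which matches the Participants section: "The total enrollment is anticipated to be 60 adolescents". The result is reported as follows: "a medium effect (*f* = .25), the power achieved was .55". The only other power statement, above .95, concerns the latent growth curve model.

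The Efficacy analysis section sets out the five-occasion model and adds "We will also evaluate the condition (treatment) × time interaction". It then says that the initial analyses will concentrate on change from pre to 4 weeks after discharge. Later assessments are each to be compared with baseline as planned comparisons, and the section comments: "This will allow us to retain the most amount of power".

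Under Outcomes, retention is judged over the 6 months of follow-up: "Ideally, we would have a dropout rate < 25" per cent.

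**The concern.** The analysis to be run first compares two occasions, and the document gives no power for it. The figure it does give is for a different test, on complete data, although the plan itself expects some loss. A reader may well carry .55 over to the 4-week result.

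This matters because the efficacy results have a role in the decision on a larger trial. The Discussion says that scaling up may not be feasible if the secondary outcomes show no trend between usual care and the experimental groups and two sites would be needed. Whoever weighs a null 4-week result needs to know how often this design would miss a real medium effect in that comparison.

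**Working it through.** **Inputs.** From Power analysis: k = 3 groups, N = 60, m = 5 occasions, f = .25 (f² = .0625), α = .10. From Efficacy analysis: the initial contrast uses m = 2 occasions, taken as baseline and 4 weeks. From Outcomes: a dropout ceiling of 25%, so 60 × .75 = 45 remain at the limit.

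**Formula.** For the group-by-time test (Pillai's V, O'Brien-Shieh noncentrality):
- s = min(k − 1, m − 1)
- df1 = (k − 1)(m − 1)
- df2 = s[N − k − (m − 1) + s]
- λ = N·s·f²
- power = P(noncentral F(df1, df2, λ) > the 90th centile of F(df1, df2))

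**Step 1: the plan's own figure.** With m = 5 and N = 60: s = 2, df1 = 8, df2 = 2(60 − 3 − 4 + 2) = 110, λ = 60 × 2 × .0625 = 7.5. Power is .551, which matches .55. Among the variants tried, only this one gives .55 without a correlation that the document does not state.

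**Step 2: the same test at the dropout limit.** With m = 5 and N = 45: df2 = 2(45 − 3 − 4 + 2) = 80, λ = 5.625. Power is .432. The fifth occasion is at 6 months, so the 6-month ceiling applies directly here.

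**Step 3: one-way comparison of the pre to 4-week change, f = .25 on the change score.** Here s = 1, df1 = 2, df2 = N − 3, λ = .0625N.
- N = 60: λ = 3.75, power .504
- N = 45: λ = 2.81, power .408
- N = 46 (just under 25% lost): λ = 2.875, power .415

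**Step 4: can .55 and .50 be compared?** Pillai's V equals s·f²/(1 + f²). With s = 2 it is .125/1.0625 = .118; with s = 1 it is .0625/1.0625 = .059. Fixing f therefore halves the effect when going from five occasions to two. At N = 60 with two occasions:
- holding V at .118: f² = .1176/.8824 = .1333, λ = 8.0, power .80 (.68 with N = 45)
- holding λ at 7.5: power .77

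The ordering depends on which quantity is held fixed.

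**Step 5: baseline adjustment at 4 weeks.** With equal variances σ² and correlation ρ, the error variance of a change score is 2σ²(1 − ρ), and after baseline adjustment it is σ²(1 − ρ²). The ratio is (1 + ρ)/2. The document gives no ρ, so these values are assumptions. Then λ = .0625N/ratio, df1 = 2, df2 = N − 4. The last two columns give power.

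| ρ | ratio | N = 60 | N = 45 |
|---|---|---|---|
| .3 | .65 | .67 | .55 |
| .5 | .75 | .61 | .50 |
| .7 | .85 | .56 | .46 |

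Each row keeps the between-group effect that gives f = .25 on the change score.

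**The case against.** The power section does not mislabel its figure. It names the mixed MANOVA, five repeated measures and 20 per group, and that is the model the efficacy section specifies first. This stands: .55 is correct for its test, and the gap lies in what is left unstated for the contrast analysed first.

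A reader might infer from .55 against .50 that the two-occasion test is weaker and that the sentence about retaining the most power is wrong. The document does not support that. Step 4 shows that the drop comes from the effect-size scaling; with the effect held constant, a focused test on 2 numerator degrees of freedom can beat one on 8. The sentence also directly follows the one about planned comparisons with baseline, and is naturally read as a remark on that restriction. It need not be deleted.

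A reader might also take .41 as the expected power at 4 weeks. The 25% ceiling covers 6 months and is an ideal for judging feasibility, so 45 at week 4 would require the whole allowance to be lost in the first month. The Missing data section also mentions multiple imputation as an alternative to complete cases. So .41 is a worst case.

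Other readings of the lead analysis give other figures. On the same convention, a joint MANOVA of the three change scores would have .61 with 60 and .48 with 45. A test over baseline, discharge and 4 weeks would have .68, although Table 4 schedules no accommodation scale at discharge. This is a further reason to state which test and which effect a power figure refers to.

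Finally, feasibility is the primary aim, efficacy is exploratory and the article is open about low power. That limits the weight of the point but does not remove it, given the part that secondary outcomes play in the scale-up decision.

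**Conclusion.** The point holds in limited form. The .55 is right for the five-occasion test with 60 complete participants; at the plan's own dropout limit that test has about .43. The pre to 4-week contrast has no stated power. With f = .25 defined on the change score it is about .50 with everyone retained, falling towards .41 as a floor. These figures assume one outcome at a time, complete-case analysis and equal groups. Even with full retention, a medium effect so defined would be missed about half the time. The sample size and the feasibility conclusions are unaffected; what changes is how a null efficacy result should be read.

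**What to change.** 1. In Power analysis, label .55 as the five-occasion group-by-time figure with complete data, and add about .43 at 25% dropout.
2. State power for the pre to 4-week contrast: about .50 with 60, lower with dropout, .41 as the worst case. Say that f = .25 refers to the change score.
3. Analyse the 4-week value adjusted for the baseline already collected, in place of a raw change score. At ρ = .5 this cuts error variance by 25%; the range of resulting power is in the table above.

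The cost is some rewording, a slightly less favourable stated power and one covariate per model. No extra participants or assessments are needed.

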## Discussion

The current study is a pilot and feasibility study that examines the implementation of CRT on a medical unit in a large children’s hospital. The description of this protocol followed SPIRIT guidelines [53, 54]. CRT + TTP is compared to treatment as usual and a CRT + contact control group (CRT + FFT). As this is a pilot and feasibility study, we have specified the outcomes we would use in a larger, randomized clinical trial. We plan to focus on the viability of integrating CRT into clinical care, refine recruitment procedures and estimate recruitment rate for a larger trial, and pilot the feasibility of the assessment strategy. Inpatient hospitalization presents as a unique opportunity for us to examine our primary outcomes of interest and establish the feasibility of this type of intervention in the context of a medical unit. Scaling this study up for a larger trial will be feasible if CRT is able to be delivered with little interruption to clinical care, if study interventions are not perceived as burdensome to staff or families, and if participants are able to be successfully recruited and retained through the follow-up phase. By evaluating our rate of enrollment and follow-up and the % of treatment completers, we should be able to determine how long it would take to enroll enough treatment completers to have a fully powered trial. If it would take 3+ years to recruit enough participants from one site, we would need to consider if it feasible to scale up the study or if a multi-site study is needed. The secondary aims could help to inform this—particularly if we see trends in a positive direction. If there is no trend for a difference between TAU and the experimental groups on secondary outcomes and it would take a two-site study to complete, scaling up of this work may not be feasible.

The study intervention builds upon prior research on the use of CRT as an adjunctive treatment for AN. In particular, this study uses CRT as a pre-treatment intervention. While increases in cognitive flexibility are typically the primary outcome of CRT, we posit that CRT may be particularly useful in increasing willingness to engage in treatment upon discharge from the hospital. In addition to assessing stages of change, we are also examining the rate of weight gain when discharged.

Family-based treatment is the only empirically supported treatment for AN; one hypothesized mechanism of action is a reduction in parental accommodation of symptoms [13, 14]. We believe that by adding a parent involvement component to CRT, it will increase parents’ awareness of their child’s cognitive style and could contribute to a reduction in symptom accommodation post-discharge from the hospital. The “Teach the Parent” component of CRT added is a novel addition to current work being done utilizing CRT. This model is particularly suited to hospital stays as youth and their parents often have down time while in hospital. Conducting CRT with their parents allows children to practice skills they learned in their own CRT session, provides them with the time to interact with parents (without a focus on why they are in hospital), and helps to teach parents about their and their child’s cognitive flexibility. Our hope is that by increasing parental awareness of the process of their and their child’s thinking they will be able to persist in re-nourishment, despite the increasing intensity of symptoms that adolescents may experience once they are discharged and living at home.

As a considerable strength of this pilot study, the methods used (recruitment, assessment, randomization, intervention, and follow-up) are being piloted in an actual clinical, real-time hospital setting. There are no restraints on the type of treatment that adolescents will discharge to, although the majority of adolescents in CHOP’s program do enter outpatient treatment. In addition, details regarding the medical care that adolescents receive (TAU) have been detailed in a prior publication [51]. Results from this study will inform a larger clinical trial to determine the effectiveness of CRT as a pre-treatment intervention, particularly with the inclusion of a parental involvement component. Our outcomes (changes in willingness to engage in treatment, rate of weight gain, and parental accommodation of symptoms) are novel for CRT studies. Although not of primary interest, we are collecting additional data on cognitive flexibility and will track changes that occur in participants’ level of flexibility over time. In general, this pilot study will inform a larger trial that will significantly add to the literature on the use of CRT with adolescents with AN.

## Abbreviations

AN: Anorexia nervosa
CHOP: Children’s Hospital of Philadelphia
CRT: Cognitive remediation therapy
FFT: Family Fun Time
IRB: Institutional Review Board
LGCM: Latent Growth Curve Modeling
TAU: Treatment as usual
TTP: Teach the Parent
